### Sample size

As our study is a pilot study applying a pre-post design, a power analysis to determine sample size was not indicated. To assess use and usefulness of the MyBraincoach app, a sample size of n=75 is deemed sufficient to obtain data of n=60 participants for analyses at follow-up, expecting a dropout rate of 20%.

### Data management

Information necessary to assess success and feasibility of recruitment will be assessed by the research team at the study centre, using standardised custom-made forms. Download and use of the app, including information on specific app features and number of interactions with the app, will be assessed using meta-data, provided by the web-design agency Indicia Betawerk, responsible for development and hosting of the app. Baseline and follow-up assessments will be conducted online using Limesurvey software. Secured hyperlinks to the baseline and follow-up assessment will be sent via email to all individuals who provided online informed consent to participate.

Safeguards will be implemented to prevent unauthorised changes of data (passwords, access rights), and only researchers entrusted with data handling, reimbursement of participants and analyses within the project will have access to the data. Source documents and data management procedures will be maintained readily available. Quality of data (eg, data from online assessments, documents regarding study and participant management, etc) will be monitored continuously. Data protection laws, such as the European General Data Protection Regulation, will be followed and every person having or requesting access to the data is obliged to confidentiality. All personal information of participants will only be documented for the duration of the study and will be saved separately from meta-data and data collected at the baseline and follow-up assessments, complying with data protection laws. Account data needed for reimbursement of participants will be deleted immediately on completion of reimbursement. Personal identification data of participants will be saved on a central server restricted by password access after assigning a randomised pseudonym ID to each participant. All analyses conducted within the project will solely use de-identified, pseudonymised data.

Meta-data, for example, on number of app downloads, logins and interactions with the app, are stored on a secured server in the Netherlands. Data are transferred using a Secure Sockets Layer certificate and will only be stored in a pseudonymised fashion to ensure participant anonymity. On signing the informed consent, participants will further be informed of the modes and purposes of data collection, storage and usage, as well as their rights to demand correction or deletion of their data.

### Data analysis plan

#### Quantitative analyses

All acquired data will be examined for potential inconsistencies and missing values. Drop-out analyses will assess potential systematic biases between participants who complete the follow-up assessment 12 weeks after baseline and non-completers, using χ² and two-sample t-tests, as appropriate. Success and feasibility of recruitment, retention of participants, use and usability of the app as well as reasons for dropouts will be described using means (SDs) and percentages, as appropriate. Changes in LIBRA, dementia literacy, health-related quality of life, self-efficacy and motivation for behaviour change will be described using dependent samples t-tests. The significance level of all analyses will be set to p<0.05 (two-tailed). Analyses will be conducted using Stata/SE V.16.0. Results will be reported according to the extended guidelines of the CONSORT statement for pilot and feasibility trials.^30^

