### Recruitment

Participants will be recruited primarily online using convenience sampling. To mitigate the risk of recruiting a predominantly highly educated and health-literate sample, a broad and diversified recruitment strategy will be employed. Recruitment channels will include advertisements in health-related and general-interest online forums and magazines, community newsletters, volunteer registries, social media channels of Leipzig University and other research institutions or non-governmental organizations, as well as community health centres and GP practices. Additional recruitment efforts will target platforms and settings with broader sociodemographic reach. Interested individuals will click on a link leading to the study homepage, where they will be able to sign an online informed consent form and provide their contact information. Eligible participants will then receive a personalised QR-code via email to download the app to avoid non-participants downloading the app, as well as a link to the baseline assessment to complete online. Questionnaire data and app metadata will be linked via a unique pseudonymised study ID embedded in the personalised survey links and stored in the app at first login. Participants will be reimbursed with 20€ for their efforts.

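### With about 15 non-completers, the planned drop-out tests will usually miss moderate attrition differences, and the named paired analyses describe only participants with both assessments

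*Protocol article*

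**What the plan says.** The protocol article, under Sample size, holds that "a sample size of n=75 is deemed sufficient" in order "to obtain data of n=60 participants for analyses at follow-up", with 20% dropout expected.

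Under Quantitative analyses, "Drop-out analyses will assess potential systematic biases between participants who complete the follow-up assessment 12 weeks after baseline and non-completers". The methods named for this comparison are chi-square tests and t-tests for two independent groups, to be chosen as each variable requires. The two-sided 0.05 level in that section covers all analyses, so it covers these comparisons too. The same section examines change in LIBRA, dementia literacy, quality of life, self-efficacy and motivation with dependent-samples t-tests, and the abstract adds McNemar's tests. Missing values are to be examined. App use is summarised with means and percentages.

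Under Recruitment, "Questionnaire data and app metadata will be linked via a unique pseudonymised study ID". Table 1 lists downloads, interactions, modules and topics among the app metadata. None of these depends on completing the follow-up questionnaire, and someone who never logs in is identifiable as a non-user.

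**The concern.** The check that the article names for attrition bias is a set of significance tests with about 15 people in one group. Such tests have little chance of detecting moderate differences, so their result says little about who has been lost. A dependent-samples t-test or McNemar's test needs both measurements, so the named change analyses leave out non-completers by construction.

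Selective dropout is plausible on the protocol's own evidence. The Introduction reports 56% app use in the earlier Dutch study in community-dwelling adults, and the Intervention section notes lower uptake of eHealth tools in people with less education. That dropout follows use is an assumption, but a reasonable one. If users both stay and improve more, the completers' mean change is higher than that of the enrolled sample. The abstract says the results will inform the design and sample size of the later RCT, so it matters whom they describe. Usability and usefulness, which are key feasibility outcomes, are also measured only at follow-up.

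**Working it through.** **The plan's own figure.** 60 / (1 − 0.20) = 75, which reproduces the stated sample size. Non-completers: 75 − 60 = 15.

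**Power of the t-test, 60 v 15, two-sided 0.05.** The standard error of a standardised difference is √(1/60 + 1/15) = 0.289, and the critical t on 73 degrees of freedom is 1.993. For d = 0.5 the noncentrality is 0.5/0.289 = 1.73. The protocol gives no effect size for this comparison, so d is varied as an assumption:

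| True difference (SD) | Power (noncentral t) |
|---|---|
| 0.2 | 10% |
| 0.3 | 18% |
| 0.5 | 40% |
| 0.8 | 78% |

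Power reaches 80% at 0.82 SD. If the number of non-completers out of 75 differs from plan, power at 0.5 SD is 26% with 8, 49% with 22 and 55% with 30.

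**Power of the chi-square test, 60 v 15 (exact enumeration, uncorrected test; proportions assumed).**

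| Completers | Non-completers | Power |
|---|---|---|
| 50% | 30% | 30% |
| 30% | 50% | 33% |
| 20% | 40% | 39% |
| 50% | 20% | 60% |
| 50% | 10% | 89% |

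**What an interval would show.** The 95% half-width for a standardised difference is about 1.993 × 0.289 = 0.58 SD. An observed difference of zero would remain compatible with true differences of more than 0.5 SD in either direction.

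**Size of the bias in the completers' mean.** Bias = (share of non-completers) × (gap between completers and non-completers) = 0.20 × gap. If the gap lies in the change score, 0.5 SD gives 0.10 SD and 0.8 SD gives 0.16 SD. The standard error of a 60-pair mean change is 1/√60 = 0.129 SD, so these biases are about 0.8 and 1.2 standard errors.

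**Illustration.** Only the 56% comes from the documents; the rest is assumed. Users change by 0.5 SD and non-users by 0. All users and 54.5% of non-users are retained.

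- Enrolled: 42 users and 33 non-users. Mean change is 0.56 × 0.5 = 0.28 SD.
- Completers: 42 users and 18 non-users, so 70% users. Mean change is 0.70 × 0.5 = 0.35 SD.
- Bias: 0.35 − 0.28 = 0.07 SD. This is 25% of 0.28, and 0.07/0.129 = 0.54 standard errors.
- Chi-square test on app use, 42/60 v 0/15: z = 0.70/√(0.56 × 0.44 × (1/60 + 1/15)) = 4.9, so it is plainly significant.

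**Which adjustment works (simulation of this scenario).** Multiple imputation including app use returned 0.28, with the standard error rising from 0.132 to 0.139. A mixed model of baseline and follow-up with app use only as a main effect left the change at about 0.34. A time-by-use interaction averaged over the enrolled use distribution returned about 0.28.

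**The case against.** A reader might infer that large bias will pass as no difference and go uncorrected. The documents do not support that, for these reasons, all of which stand:

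- A difference of 0.8 SD is detected 78% of the time and a 40-point difference in proportions 89%. Moderate differences are the ones usually missed.
- In the illustration, a test on app use would flag the dropout in essentially every run. The protocol does not restrict which variables are compared, so app use could be among them.
- The protocol nowhere says that a non-significant test will be taken as absence of bias, or that the change analysis depends on it.
- Missing-data methods may sit in a statistical analysis plan that is not shown. Their absence from a condensed article is not an error.
- The wording of the test choice leaves room for an exact test. Small expected counts (below 5 in a group of 15 when prevalence is under one third) are therefore not a separate fault.
- The change outcomes are exploratory and the study is stated not to assess effectiveness. Recruitment, retention and reasons for dropout are reported descriptively and do not rest on these tests.

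This limits the weight of the point but does not remove it. The tests are the method chosen for assessing systematic bias, and with the planned numbers they are uninformative over the moderate range.

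**Conclusion.** The point holds in a limited form. With the protocol's own 60 v 15 split, the drop-out tests have about 40% power at 0.5 SD and about 30 to 40% for 20-point differences in proportions. Non-significance therefore cannot exclude selective dropout. The named paired analyses describe people with both assessments, although data that could extend them to all enrolled are already collected and linked.

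The power figures rest on 20% dropout and the stated significance level. The size of any bias rests on assumptions about how use, retention and change relate. It is 0.07 SD in the illustration, and at most 0.16 SD for a gap in change of up to 0.8 SD. With exploratory outcomes, this is a minor improvement and no threat to the study's feasibility aims.

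**What to change.** In Quantitative analyses:

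1. Report completer versus non-completer standardised differences with 95% confidence intervals, for baseline variables and app use, instead of relying on p-values.
2. State that the paired tests describe participants with both assessments.
3. Add an estimate of change for all participants with baseline data. Use either multiple imputation including the baseline value, app use, age, sex and education, or a mixed model with a time-by-app-use interaction averaged over the enrolled use distribution. App use as a main effect alone is not enough.
4. Show the completer-only result alongside.

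The cost is a little extra analysis, with no new data. The all-enrolled estimate assumes data are missing at random given app use and the baseline variables. Intervals will be slightly wider: a standard error of 0.139 against 0.132 in the illustration, about 5% (0.139/0.132 = 1.05).

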#### Qualitative analyses

A single remote, video-based focus group targeting n=8 participants will be conducted as a formative supplement to the quantitative feasibility assessment. The focus group is intended to provide exploratory insights into app use and usability and identify suggestions for intervention refinement, rather than to achieve thematic saturation. A researcher experienced in group interviews will moderate the focus group (expected duration: 90–120 min), which will be conducted using appropriate software (eg, Zoom). The interview guide will be designed following the guidelines for problem-centred interviews,^42^ a semi-structured type of interview aiming to provide impulses for discussion and free narration of participants. Topics to be covered include previous experience with eHealth/mHealth tools, previous knowledge of lifestyle factors relevant for dementia risk reduction, perception of app-design, use and usability of specific app-features, evaluation of app content and suggestions for improvement, using open-ended questions. The focus group will be video-recorded and transcribed fully by an experienced transcribing service.

Content of the focus group will be analysed using structured content analyses.^43^ First, categories will be built inductively to analyse interview transcripts (coding scheme). Second, transcripts and derived categories will be entered into MAXQDA software. Finally, blocks of transcripts will be assigned to the coding scheme. Results will be processed quantitatively in MAXQDA. Sociodemographic information of focus group participants (age, sex, education) will be analysed descriptively using Stata.

### Patient and public involvement

Usability testing sessions, particularly targeting people with lower degrees of education and with disabilities, are an integral part of the study and will be conducted before the pilot study to ensure accessibility of the intervention across various backgrounds of participants and gather participant feedback. Further, we aim to gain a better understanding of user experiences with the app and gather potential suggestions for improvement by means of a moderated focus group following completion of the pilot study. This approach will increase participant involvement in the design of the intervention to be tested in a subsequent confirmatory RCT, including implementation of suggested changes and adaptations to the app, if feasible.

## Ethics and dissemination

###  Ethical approval

The study was approved by the Ethics Committee of the Medical Faculty of Leipzig University (ref.: 476/22-ek).

### Consent to participate

All participants in the pilot study will provide online informed consent to participate prior to participation, using an electronic Transport Layer Security-encrypted consent form. Potential participants will be informed about details of the study, voluntariness of participation, the option of discontinuing participation at any time and details on data protection. Usability testers will sign a written informed consent form prior to the usability testing session. Participants having agreed to be re-contacted after the pilot study and willing to participate in the focus group will sign an additional online informed consent prior to participation in the focus group.

### Adverse events

We will investigate a mHealth intervention targeting general lifestyle behaviour to reduce dementia risk. By providing individuals with personalised feedback on their individual risk profile for dementia, the intervention might raise fear or concern among participants to some degree. However, this risk is deemed very low, as participants will be informed about the study aims before consenting to participate, that is, a general interest and willingness to engage with the topic can be assumed. As the intervention targets everyday behaviour beneficial for a healthy lifestyle, is aimed at generally healthy individuals and advice within the app will suggest consulting a GP in case of uncertainty, potential harm for participants is deemed negligible. Potential adverse events occurring during the pilot study will be assessed, regardless of a causal link to the study. Participants will be able to document any problems arising during use of the study within the app. Contact details of the research team will be placed prominently within the app and participants will be asked to contact the research team whenever encountering problems regarding study participation and/or app use.

### Dissemination plan

The results of this study will be disseminated at conferences and in publications in peer-reviewed scientific journals, published open access where possible. All reported data will not allow for inference to study participants, but will be reported anonymously. Study design and progress, as well as results, will also be disseminated using social media (eg, X, LinkedIn) to inform the general public. The participant-level dataset will not be made publicly available due to data protection and consent restrictions.
